### Description of measures taken to avoid bias

Given the context, blinding workers, physicians, and assessors is impossible. To control bias arising from the absence of blinding, we propose using a modified version of Zelen’s design. This makes it possible to prevent the risks of bias caused by the absence of blinding, because in conventional randomized trials workers assigned to the control group may withdraw from the trial more easily, try to receive the study treatment, or change their behavior when the endpoint is being assessed. The primary endpoint was blind evaluated.

The risk of contamination in the usual-care group is highly unlikely because our short spa therapy program is not currently offered outside of this study.

The risk caused by revealing the study hypotheses to workers is reduced by restricting contact between the patients of the two groups.

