### Instruments

The primary endpoint is the score on the Quick DASH scale at 3 months. The Quick DASH (Disability of Arm-Shoulder-Hand) is a self-administered questionnaire which measures the physical disability and symptoms for all upper limb disorders in an heterogeneous population and for acute as well as chronic disorders [22]. It contains various domains such as handicap, activity of daily living, pain during activities, strength. It has good psychometric properties with a Cronbach’s alpha coefficient of 0.89 and an intra-class correlation coefficient of 0.94 which suggests excellent test-retest reliability. We assessed functional capacity monthly over 6 months.

Secondary endpoints are:The areas of pain and intensity of the discomfort or pain are assessed using the Nordic questionnaire [21] and a numerical pain scale.Overall psychological status is assessed using the Hospital Anxiety and Depression Scale by Zigmond and Snaith [23].The SF-36 questionnaire is used for patient quality of life [24].Duration of sick leave accumulated during the study period.Use of analgesics.

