### Ethical consideration

All workers will receive their written consent form, which they will sign all with the physician during the inclusion medical visit. The study will be conducted in accordance with the principles of the Helsinki declaration. This protocol was approved by the Sud-Est VI medical ethics committee of the University Hospital of Clermont-Ferrand, France, institutional review board (reference: AU 1206 – IRB no: IRB00008526) on July 3, 2015, as well as by the French National Agency for Medicines and Health Products Safety on August 14, 2015.

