The various people in charge of the spa therapy who are responsible for conducting the intervention in this study, have more than 3 years of clinical experience and have been specifically trained in implementing the protocols by means of a detailed handbook that precisely describes each intervention illustrated with photographs and diagrams from the video program given to workers [27].

During the inclusion visit, control-group workers will be given the same folder as the intervention group, with the seven exercise sheets and USB key. The workers are not given guidance on the performance of any exercise that may have been determined by the conduct of the clinical examination. They will perform home program (exercises and relaxation) during the first three months and then the spa therapy of 6 consecutive days identical to the intervention group.

Intervention and control-groups workers will receive unrestricted pharmacological or non-pharmacological usual care from their physicians or specialists, such as analgesics, physiotherapy or orthosis, over 6 months. However, any medication taken during or after the intervention must be declared and reported in the patient follow-up questionnaires.

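### The primary endpoint is described as evaluated blind, but it is a self-completed QuickDASH in an unblinded trial, and the Zelen design is credited with more protection than its stated reasons support

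*Protocol article*

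**What the plan says.** Protocol article, Description of measures taken to avoid bias. The section opens by saying that "blinding workers, physicians, and assessors is impossible". It then proposes a modified Zelen design and says of it: "This makes it possible to prevent the risks of bias caused by the absence of blinding". The reasons given concern workers assigned to control: they might drop out more readily, seek the study treatment, or behave differently at assessment. The paragraph ends: "The primary endpoint was blind evaluated". The section adds that limiting contact between the two groups reduces the risk from workers learning the study hypotheses.

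Instruments. "The primary endpoint is the score on the Quick DASH scale at 3 months". The QuickDASH "is a self-administered questionnaire which measures the physical disability and symptoms for all upper limb disorders".

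Conduct of the study. Endpoint questionnaires from day 6 onward go out by mail, with mail or telephone reminders.

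Sample size determination. Returned questionnaires are scanned. No separate outcome assessor is described anywhere in the article.

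**The concern.** Two statements in one paragraph cannot both be true of this endpoint. For a self-completed scale, the person who evaluates the outcome is the participant. A worker who attended six consecutive days of spa therapy and self-management sessions knows it, so the score cannot be blind in the intervention arm.

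The statement matters because QuickDASH is a subjective score and the comparison is between workers who have had an intensive programme and workers who have had usual care plus a home folder. Expectation and willingness to report improvement can move such a score in favour of the programme. A reader or risk-of-bias assessor who takes the blinding statement at face value would rate the result as better protected than it is. The Abstract and Discussion both present the trial as able to give evidence of a good level, so the error bears on what the trial may conclude.

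The Zelen sentence adds to the problem. It claims prevention of the bias that comes from lack of blinding in general, while its reasons address one part of that bias.

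**Working it through.** **Step 1. Who rates the endpoint?**

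| Item | Protocol article section | Content |
|---|---|---|
| Primary endpoint | Instruments | QuickDASH at 3 months |
| Rater | Instruments | the worker (self-administered) |
| Collection | Conduct of the study | by mail, with reminders |
| Processing | Sample size determination | scanned |
| Blinding of workers | Description of measures taken to avoid bias | impossible |
| Blinding of the endpoint | same section | claimed |

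The rater is the worker, and the worker is unblinded by the article's own account. The only people left who could be blinded are those who handle or analyse the forms, and they do not produce the score. The claim therefore fails on any reading that refers to the rating itself.

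**Step 2. What do the Zelen reasons cover?** All three (withdrawal, treatment seeking, changed behaviour at assessment) are reactions of control workers. None concerns a treated worker's expectation of benefit. The article elsewhere uses weaker language than prevention. The hypothesis-disclosure risk is only reduced, and Sample size determination allows for a possible Hawthorne effect in the delayed group.

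**Step 3. The plan's own sample size, for the inputs.** SD 18, difference 12, two-sided 5%, power 90%:

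- n per arm = 2 × (1.960 + 1.282)² × 18² / 12² = 47.3, so 48.
- With 20% loss: 48 / 0.8 = 60 to enrol per arm.
- The stated 75 is reached if the Hawthorne allowance, which has no stated size, cuts the difference to about 10.7. Then n = 60 and 60 / 0.8 = 75. The 10.7 is back-solved, not stated.

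The gap between 60 and 75 errs on the safe side and is not evidence for this point. It is shown only because the next step uses the same SD and the evaluable number 75 × 0.8 = 60 per arm.

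**Step 4. Illustration of what reporting bias could do.** The bias sizes are assumptions; the documents give none. Assume no true effect.

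- SE of the difference = 18 × √(2/60) = 3.29.
- Chance of a significant result favouring spa = P(Z > 1.96 − bias/SE).

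| Assumed bias (points) | bias/SE | Significant, favouring spa |
|---|---|---|
| 0 | 0 | 2.5% |
| 2 | 0.61 | 8.8% |
| 3 | 0.91 | about 15% |
| 5 | 1.52 | about 33% |
| 6 | 1.83 | 44.7% |

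For scale, the planned difference is 12 points. Recruiting more workers does not help: it shrinks the SE and leaves the bias where it is.

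**The case against.** **The Zelen design does some work.** If control workers do not know of the immediate-spa arm, disappointment, drop-out and treatment seeking can be less. Those are the mechanisms the article names, and it also restricts contact between groups. This stands. A reader might infer that the claimed protection does not exist at all, or that controls knowingly wait for their spa week when they complete the 3-month form. The documents support neither. They say the intervention is offered to controls at least 3 months later, but not what controls are told or when, and the flow chart is not shown. A control worker may know what care he or she receives without knowing that it is the control condition.

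**Blind evaluation may refer to data handling or analysis.** Possibly so. The sentence would then still need rewriting, because it speaks of the endpoint and would be read as the rating.

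**The order of steps at inclusion is a matter for the full protocol.** This also stands. Consent is a form "which they will sign all with the physician during the inclusion medical visit", and "During the inclusion visit, control-group workers will be given the same folder", so allocation is acted on at that visit. A reader might infer that baseline QuickDASH, which is the ANCOVA covariate, is completed after allocation is known, or that workers are selected after allocation through consent. The article shows neither. It is condensed, the detailed order of the visit is commonly left to the full protocol, and an intention-to-treat analysis is specified. Only a request for confirmation is justified.

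**The percentages rest on assumed biases and would apply to any open-label self-report trial of this size.** Correct. They show why the label matters. They do not measure a gain from the fix, since rewording does not alter what workers report.

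**Conclusion.** The point holds as a misstatement of the design. The primary endpoint is an unblinded, participant-reported outcome, and the article should not call it blind evaluated. That conclusion needs no assumption, because it follows from the article's own text. The claim that the Zelen design prevents bias from absence of blinding is too broad: as justified, it extends to possible reduction of control-arm reactions and no further. How far even that works cannot be judged from the article.

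The size of any resulting bias is unknown. Under the stated assumptions (SD 18, 60 evaluable per arm, no true effect), 3 to 5 points of differential reporting would raise the chance of a false positive favouring spa from 2.5% to between about 15% and 33%. The endpoint remains usable, but a positive result must be read with this in mind.

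**What to change.** 1. Delete the sentence saying that the primary endpoint was evaluated blind. If only data handling or analysis is blinded, say exactly that and name the step.
2. Describe the 3-month QuickDASH as an unblinded, participant-reported outcome.
3. Limit the Zelen claim to reducing control-arm reactions (withdrawal, treatment seeking, changed behaviour).
4. State that the 3-month difference may include expectation or reporting bias, and qualify the statement on level of evidence in the Abstract and Discussion accordingly.
5. As a query rather than a correction: confirm that eligibility and the baseline QuickDASH are recorded before allocation is disclosed.

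Items 1 to 4 are changes of wording and cost nothing in staff, procedure or sample size. They can be made although recruitment began in September 2015. Item 5 needs only an answer from the full protocol.

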### Randomization

The randomization list will be drawn up by the methodologist in charge of the project before the beginning of the trial. Randomization will be conducted so as to balance group numbers using block randomization stratified by center; this will make it possible to check patient eligibility and to communicate information on randomization to the investigator and any other correspondents for each of the workers.

### Sample size determination

To study the impact at 3 months of the 6-day standardized short thermal intervention on pain-related functional impairment measured using QUICK DASH scale (disability/symptom section), the sample size estimation is based on a comparison between both arms for a two-sided type-I error of 5 and 90% statistical power. According to the literature [26], it seems relevant to consider a standard deviation at 18 and a baseline value equaling 48 (/100) for the QUICK DASH scale. Considering (i) an assumed 25% improvement (−12 points) in favor of the 6-day standardized short thermal group, (ii) a possible Hawthorne effect (in the “delayed treatment” group), and (iii) a lost-to-follow-up rate of 20%, it is planned to include 75 patients per randomization group. Data will be entered in real time using the online clinical research data management tool REDcap (Research Electronic Data Capture). Assessment questionnaires will be data-scanned to prevent data entry risks.

#### Procedure for data collection

The study inclusion visit will enable the collection of sociodemographic parameters (age, weight, height) and job characteristics (profession, name of company, length of time in the position, stress, and interest in the position).

#### Conduct of the study

The self-administered questionnaires are repeated during the study at predetermined intervals over a period of 6 months (Fig. 2).

**Fig. 2 Fig2:**
[figure not shown]
Self administered questionnaires

Quantitative adherence (number and duration of sessions) and qualitative adherence (type and way of performing the intervention) will be systematically evaluated using monthly follow-up self-administered questionnaires [27, 28].

The assessment of endpoints on day 6 and then monthly over 6 months will be conducted by sending self-administered questionnaires by mail. Reminders and follow-up will be by mail and by telephone calls if necessary.

### Ethical consideration

All workers will receive their written consent form, which they will sign all with the physician during the inclusion medical visit. The study will be conducted in accordance with the principles of the Helsinki declaration. This protocol was approved by the Sud-Est VI medical ethics committee of the University Hospital of Clermont-Ferrand, France, institutional review board (reference: AU 1206 – IRB no: IRB00008526) on July 3, 2015, as well as by the French National Agency for Medicines and Health Products Safety on August 14, 2015.

### Intervention protocol

The spa therapy and individualized self-management interventions have been put together by a steering committee and then standardized so as to be the same in the different centers participating in the study. The steering committee, which comprises investigators, treatment managers, physiotherapists, sports instructors, and psychologists, was in charge of the standardization and reproducibility of the intervention for all the centers.

Meetings with all the steering committee members were organized to find a consensus on the treatment protocol, which describes in detail the content and organization of the intervention while keeping in mind the circumstances and expertise of the different centers involved in the study. This content was approved by means of a feasibility study before the study began. The content of the intervention is defined both in the written protocols, which are illustrated with photographs, and in digital format as a USB key, with recordings from the feasibility assessment week (Fig. 3, Additional file 1: Figure S1, Additional file 2: Video S1).
**Additional file 2: Video S1.** Cervical spine stretch video. (MP4 46804 kb)

**Fig. 3 Fig3:**
[figure not shown]
Intervention

Intervention-group workers will receive the spa therapy at the beginning of the study. After the spa therapy, workers will continue their home exercise program up to the end of the study.

Concerning the spa therapy, they will receive 2 h of intensive therapy for 6 consecutive days: 1 h of spa therapy, a break of 15 min, and a 45-min self-management session. The spa therapy will be outside the working hours. Study workers were not mixed with the general public in the spa center.

Spa mineral water and treatments are approved and controlled by the French authorities (Table 2). Treatment included: mineral hydrojet sessions at 37 °C for 10 min, manual massages of upper-limbs under mineral water at 38 °C for 10 min, applications of mineral matured mud at 45 °C to the upper-limbs for 15 min and supervised general mobilisation in a collective mineral water pool at 32 °C in groups of seven patients for 15 min.

**Table 2 Tab2:** Spa therapy treatments

Description	Duration	Conducted by
Underwater massage bath	10 min	Spa therapist
Underwater jet massage with focused massaging of the area of pain	10 min	Spa therapist
Mud wraps or similar (poultice)	15 min	Spa therapist
Hydrotherapy session	15 min	Spa physiotherapist

The treatments are prescribed during the study inclusion visit and are tailored based on the areas of pain identified during clinical examination. They are performed by spa therapists and physiotherapists.

The self-management program consists of sessions of physical exercises out of the water without any special equipment. It is run by a physiotherapist or adapted physical activities instructor on days 1, 3, and 5. The physical activity sessions alternate with counseling with a psychologist on pain management and relaxation on days 2, 4, and 6.

Workers also receive a folder containing sheets with physical exercises adapted to their condition so that they may continue a stretch break program after the course of treatment, relaxation exercises that they can perform themselves, as well as a full program of health activities on a USB key. The sheets in this folder are illustrated with photographs and detailed descriptions of the exercises to perform. The most relevant exercises for each worker will have been individually determined during the week of treatment.

The various people in charge of the spa therapy who are responsible for conducting the intervention in this study, have more than 3 years of clinical experience and have been specifically trained in implementing the protocols by means of a detailed handbook that precisely describes each intervention illustrated with photographs and diagrams from the video program given to workers [27].

During the inclusion visit, control-group workers will be given the same folder as the intervention group, with the seven exercise sheets and USB key. The workers are not given guidance on the performance of any exercise that may have been determined by the conduct of the clinical examination. They will perform home program (exercises and relaxation) during the first three months and then the spa therapy of 6 consecutive days identical to the intervention group.

Intervention and control-groups workers will receive unrestricted pharmacological or non-pharmacological usual care from their physicians or specialists, such as analgesics, physiotherapy or orthosis, over 6 months. However, any medication taken during or after the intervention must be declared and reported in the patient follow-up questionnaires.

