#### Statistical analysis

Statistical analysis will be conducted on the intention-to-treat population using Stata software, V.13 (StataCorp, College Station, Texas, USA). A two-sided P value of less than 0.05 will be considered for statistical significance. Baseline characteristics will be presented for each randomized group as the mean ± standard deviation or median (interquartile range) according to the statistical distribution for continuous data, and as the number of patients and associated percentages for categorical parameters. Comparisons between randomized groups will be analyzed using the Chi2 or Fisher’s exact test for categorical variables and the Student t-test or Mann-Whitney’s test for quantitative parameters, with normality verified by the Shapiro-Wilk test and homoscedasticity by the Fisher-Snedecor test (notably for primary outcome QUICK DASH scale at 3 months). Primary analysis will be completed using (1) ancova taking into account baseline QUICK DASH as covariate as recommended by Vickers and Altman [29] and (2) linear regression model in multivariate context. Covariates used for adjustment will be fixed according to (i) univariate results and (ii) clinical relevance including (use of analgesics) stratification factors. Results will be expressed as effect sizes and 95% confidence intervals. Regarding the analysis of repeated measures, random-effect models (linear or generalized linear according to the statistical distribution of dependent variables) will be performed, as usually proposed, to study the fixed-effects group, time points, and “group x time” interaction, taking into account between- and within-subject variability. The impact of covariates (as observance) will be also studied. A sensitivity analysis will be performed to study the impact of missing data; when appropriate, they will be handled in accordance with the estimation method developed by Verbeke and Molenberghs [30].

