Having said that, the various treatments undertaken outside and within the work environment to keep workers at work or facilitate their return to work have their cost too [43]. A recent study evaluated the cost-effectiveness of three types of treatment for MSD aiming to facilitate the return to work of employees on long-term sick leave [42]. The interventions consisted of a physical activity and education intervention, a workstation intervention, or a combination of physical activity, education, and workstation assessment. This modeling approach showed that the most cost-effective intervention was physical activity and education. Given the current importance of the economic impact of chronic disorders and their treatment, our study will include a supplementary medical cost-effectiveness analysis with a societal perspective to evaluate whether it will be possible to implement our global multidisciplinary intervention [44]. Cost estimation will include direct and indirect medical costs. The cost of spa therapy will be calculated from guidelines of the French association of thermal centers. An economic analysis society’s willingness to pay for the thermal water treatment would be also measured.

The originality of this intervention lies, firstly, in its short, intensive format, which is compatible with remaining in work; secondly, in its multidisciplinary approach; and lastly, in its target population. The program is aimed at a population who are in employment at the time of treatment, so patients do not need to be on sick leave to follow treatment. This is made possible by the duration of the intervention (1 week), by the proximity of the centers to the workplace or residence of patients, and by the flexibility of treatment times relative to patients’ work schedules.

Inclusion of subjects commenced in September 2015 and will continue until February 2018. The study is projected to end in September 2018. Results should be available in February 2019.

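### Pool sessions given in groups of seven could cluster outcomes in the intervention arm only, and none of the stated analyses allows for it

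*Protocol article*

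**What the plan says.** **Delivery.** The Intervention protocol section says of the spa course that "they will receive 2 h of intensive therapy for 6 consecutive days". One component, the supervised mobilisation in a shared pool, is given "in groups of seven patients for 15 min". Of the spa users it says: "Study workers were not mixed with the general public in the spa center". Exercise sessions fall on days 1, 3 and 5 ("It is run by a physiotherapist or adapted physical activities instructor on days 1, 3, and 5"), and sessions with a psychologist on days 2, 4 and 6. The article does not say whether these sessions are given to groups.

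**Control arm.** The same section gives controls a home programme for the first three months and the identical spa course only afterwards. At the primary endpoint, Quick DASH at 3 months, controls have had no group treatment.

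**Analysis.** The Statistical analysis section names a Student t-test or Mann-Whitney test, an ANCOVA on baseline Quick DASH, and a multivariable linear regression with the stratification factors among the covariates. Randomisation is of individual workers, stratified by centre. The repeated-measures models have random effects "taking into account between- and within-subject variability". No model has a level for pool group, treatment week or therapist, and the Sample size determination section has no design effect.

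**The concern.** Workers who share pool sessions also share a supervisor, a site, a calendar period and each other's company. Any of these can make their later scores more alike than those of workers treated apart. Because controls are not grouped before month 3, the design would be partially nested, with correlated outcomes in one arm and independent outcomes in the other.

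All the stated methods take workers as independent, or allow only for repeated measures within a worker. With a positive within-group correlation they understate the variance of the intervention mean. The confidence interval is then too narrow, and a superiority claim is made at more than the stated 5% level. The error would favour the intervention. Adjusting for centre does not remove it, since each centre would treat several groups over the trial.

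**Working it through.** **Inputs from the article**
- SD 18, difference 12 points (25% of 48), two-sided alpha 5%, power 90%, 20% loss, 75 per arm (Sample size determination).
- Up to 7 workers per pool group (Intervention protocol).

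**Assumption**
- The article gives no ICC. I use 0.02, 0.05 and 0.10. For the ANCOVA, read this as the correlation left after adjustment.

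**Step 1: the plan's own figure.**
n per arm = 2 × [18 × (1.960 + 1.282) / 12]² = 47.3, so 48. Dividing by 0.8 gives 60. The article plans 75 and also cites a Hawthorne allowance to which it gives no number, so 75 cannot be reproduced from the stated numbers. That is a separate matter and does not show 75 to be wrong. For this check, 75 × 0.8 = 60 evaluable per arm, and power for 12 points without clustering is 95.5%.

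**Step 2: group size.**
75 / 7 is about 11 groups. After 20% loss, 7 × 0.8 = 5.6 evaluable workers per group. This is the main case; 7 is the upper bound.

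**Step 3: formulas, with clustering in the intervention arm only and total SD held at 18.**
- Design effect in that arm: DE = 1 + (m − 1) × ICC.
- True SE over independence SE: R = √[(1 + DE) / 2].
- Actual alpha = 2 × P(Z > 1.96 / R).
- Power for 12 points at the nominal critical value: P(Z < 12 / SE − 1.96), with SE = 18 × √[(1 + DE) / 60].

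Worked line for m = 5.6 and ICC 0.05: DE = 1 + 4.6 × 0.05 = 1.23; R = √(2.23 / 2) = 1.056; alpha = 2 × P(Z > 1.856) = 6.3%.

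| Evaluable per group | ICC | DE | R | Actual alpha | Power, 12 points |
|---|---|---|---|---|---|
| 5.6 | 0.02 | 1.09 | 1.02 | 5.5% | 94.6% |
| 5.6 | 0.05 | 1.23 | 1.06 | 6.3% | 93.3% |
| 5.6 | 0.10 | 1.46 | 1.11 | 7.7% | 90.9% |
| 7 | 0.02 | 1.12 | 1.03 | 5.7% | 94.4% |
| 7 | 0.05 | 1.30 | 1.07 | 6.8% | 92.6% |
| 7 | 0.10 | 1.60 | 1.14 | 8.6% | 89.3% |
| 3 | 0.05 | 1.10 | 1.02 | 5.6% | not computed |
| 3 | 0.10 | 1.20 | 1.05 | 6.2% | not computed |

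**Step 4: on the Quick DASH scale, m = 5.6.**
The independence SE is 18 × √(2/60) = 3.29 points, a 95% half-width of 6.4. At ICC 0.05 the true SE is 18 × √(2.23/60) = 3.47, half-width 6.8. At ICC 0.10 it is 18 × √(2.46/60) = 3.64, half-width 7.1.

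**Step 5: why the m = 3 rows are there.**
The Discussion has inclusion running from September 2015 to February 2018, about 30 months. That is 75 / 30 = 2.5 intervention workers a month, or about 1.25 per spa site with two sites, each treated in the month after randomisation. Unless enrolment was batched, pools may often have held fewer than seven intervention workers.

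**The case against.** The strongest reply is that the grouping is thin. Only 15 minutes of a two-hour daily programme are stated to be in groups. The treatments "are tailored based on the areas of pain identified during clinical examination", the exercises are chosen for each worker, and the Discussion explains that remaining at work is made possible partly "by the flexibility of treatment times relative to" work schedules. A reader might infer that the whole intervention is given to fixed groups of seven who start together, share the same staff and stay together for the week. The article does not say so. Six consecutive days and separation from the public make it plausible, no more. This part of the reply stands.

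Second, the endpoint is a mailed self-report some two to three months after the course, and the models adjust for baseline and centre. Residual correlation may therefore be small. This also stands. A reader might conclude that the planned standard errors are too small as a matter of fact, but that needs a positive ICC, and the article gives none.

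Third, groups may be smaller than seven. Intervention workers might also share a pool with delayed controls, which the article neither states nor excludes. This lowers the figures, as the m = 3 rows show. It does not cluster the controls at month 3, because their course comes later.

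Fourth, a condensed article may leave such a term to the full protocol or the analysis plan, neither of which is at hand. That is possible. But the article does more than stay silent. It names the tests and the variance components, and the structure it names omits a level that its own description of the intervention may create.

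**Conclusion.** The point holds as a conditional one. If workers treated together have positively correlated outcomes at 3 months, the stated analyses understate the standard error of the primary comparison, because the possible clustering is in one arm and no model includes it. On the main illustration (5.6 evaluable per group, ICC 0.02 to 0.10) the true standard error is about 2% to 11% larger and alpha is about 5.5% to 7.7%. Full groups of seven raise alpha to 5.7% to 8.6%. With groups of about three, it is about 5.6% at ICC 0.05. These figures rest on assumed ICCs, on stable group membership and on a normal approximation.

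A reader might also infer that the trial is underpowered or needs more workers. The figures do not support that: for the stated 12 points, power is 89% or more in every case computed up to ICC 0.10, and above 90% with 5.6 per group. If the 15 workers per arm beyond Step 1 are read as the Hawthorne allowance, the trial is sized for about 10.65 points, and with 5.6 per group power for that difference falls from 90.0% to 86.7% at ICC 0.05 and 83.2% at ICC 0.10. That reading is an inference, since the allowance has no number, and it does not by itself call for a larger sample. The matter at stake is the type I error and the width of the confidence interval.

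**What to change.** 1. Record in REDCap, for each intervention worker, the pool group attended and the treatment week. If membership changes from day to day, the record will show it, and treatment week within site can serve as the cluster.
2. For between-arm comparisons up to month 3, add a random group intercept in the intervention arm only. The alternative is cluster-robust standard errors with each control as its own cluster and a small-sample correction. At minimum, pre-specify this as a sensitivity analysis of the primary ANCOVA.
3. State that the clustering is confined to one arm only up to month 3, since controls take the spa course after that.
4. Leave the sample size as it is.

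The cost is a small addition to the data form and one model term. No treatment procedure changes. The confidence interval becomes slightly wider if the ICC is positive and barely moves if it is near zero. The group variance will be imprecise, as it comes from about 11 groups if they are full, so it should be reported with its uncertainty.
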